Following the same schedule as group A, patients from group B will receive usual medical care and osteopathic evaluation only. The osteopathic evaluation will last 10 minutes. To maintain blinding of NICU personnel, the following 20 minutes osteopaths will keep their position close to the incubator or bed without touching the infant.

Osteopathic service will be provided twice a week, on Tuesdays and Fridays.

In case of critical preterm ’s health conditions (i.e. acute infections, per-acute emergency care) or supplemental neonatal medical screening during the osteopathic service, the aforementioned intervention can be temporally stopped for a given trial participant. The infant will not be either evaluated or treated. This is in line with hospital safety procedures and primary care priority intervention.

Allocation concealment and blinding

NICU staff are unaware of study design and outcomes.

NICU staff are blinded to patients allocation, since all infants will be touched by osteopaths from group A and B

Data entering and data export

Data collection will be performed using an ad hoc locally developed software called EBOM-GCCN.

EBOM-GCCN data set is an informatics tool that improves the efficiency and accuracy of data and has been developed to assist neonatologists, nurses and osteopaths in daily patients management.

The software consists of three sections:

- Section 1: Intended for use by neonatologists and nurses for recording patients' general details and all clinical information;

- Section 2: Intended for use by “osteopaths performing the evaluation&treatment”;

- Section 3: Intended for use by “osteopaths performing the evaluation”.

Records in section 1, 2 and 3 are exclusively and respectively accessible to NICU staff, “osteopaths performing the evaluation&treatment” and “osteopaths performing the evaluation”.

Nursing and medical records will be collected daily by the NICU staff, from the time the infants enters the unit to the time of discharge.

Osteopathic records will be collected twice weekly when the osteopathic service will be provided. “Osteopaths performing the evaluation&treatment” will collect data in relation to the structural examination and the techniques applied, while the “osteopaths performing the evaluation” will only collect data for the structural examination.

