Data export will take place at the end of the study by the statistician from the coordinating center European Institute for Evidence Based Osteopathic Medicine (EBOM).

Measurements

To evaluate the effect of the treatment, standard measurements will be recorded. Data will be collected at the baseline (entry time, T0), every time the osteopathic service is provided and at the end of the stay in the unit (discharge time, T1). An expected average period of 4 weeks has been considered.

The following measurements will be included for the primary and secondary outcomes.

Primary outcome: length of stay (LOS)

LOS will be used as primary outcome and measured as the mean difference in days between T1 and T0.

According to international guidelines, the following physiological conditions are required for discharge: maintenance of body heat at room temperature, coordinated sucking, swallowing, and breathing while feeding; sustained pattern of weight gain; stability of cardiorespiratory function (no episodes of apnea/bradycardia for 2-5 days, free of supplemental oxygen support) 8.

Secondary outcomes

Secondary outcome measurements include the following parameters:

1. daily weight gain, referred as the net weight variation per day expressed in grams
2. episodes of vomit, the number of vomits per day
3. episodes of regurgitation, the number of regurgitations per day
4. episodes of stooling, the number of stools per day
5. use of enema, the number of enemas used per day
6. time to reach full enteral feeding, the number of days before autonomous feeding is achieved
7. NICU costs, calculated as NICU daily newborn expenses, according to local authorities, multiplied by the newborn’s LOS. Costs will be estimated in euros per day
8. side effects of treatment (osteopathy and clinical procedures)

In addition to these measurements, socio-demographic and clinical data will be collected and include:

1. newborn’s data: gender, gestational age, weight at birth and at entry, height, head circumference at birth, route, type and length of delivery, diagnosis at T0 and T1, associated pathologies
2. mother’s data: age, ethnicity, BMI, nationality, number of previous pregnancies, clinical medical condition during pregnancy, concurrent pathologies
3. father’s data: age, ethnicity, BMI, nationality, concurrent pathologies

Statistical analyses

All calculations will be performed at the coordinating center EBOM.

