The expected disadvantages for the intervention provided in the trial are null as well as no potential side effects due to osteopathic care are predicted as shown by the recent osteopathic literature 19. However, any side effect will be recorded during the study period and appropriately discussed in the final paper.

Publication policy

The results of the trial will be published in peer-reviewed journals and presented at relevant congresses. The trial will be reported in accordance with the CONSORT recommendations.

DISCUSSION

The purpose of this multicentre single blinded RCT is to confirm the benefits of OMT in the care of preterm infants. In this trial, osteopathic care is not based on a predetermined protocol but on needs-based approach. Thus subjects can potentially be exposed to different techniques, leading to inter-subjects and intra-subjects OMT variability. Nevertheless the objective is to provide evidence of the impact of osteopathic approach rather than the association with a given manual protocol.

On the basis of quantitative data, the scope is to estimate the effect of OMT across different centers, proving generalizability on the effectiveness of osteopathy in NICUs. Well-designed researches are scarce in the osteopathic area, thus the present study will provide the most convincing evidence of relationship between exposure and effect.

To the best of our knowledge, this will be the first study in osteopathy applied to infants using gold standards methods that include a randomized multicentre approach, a single hub computer-based data collection and a large sample size stratified by risk factors. In addition to this, the statistics that will be used will be aimed to consider different sources of variability, to allow reliable results for the effectiveness of OMT. Finally, the expected benefits for the intervention provided in the trial are shorter period of hospitalization and improvements in the secondary outcomes, leading to enhanced quality of health service delivered and cost reductions.

Authors’ contribution

CF, PG and BG conceptualized, designed and wrote the protocol. RC, D’IC, FP, PFP and TL review the protocol for important intellectual content. All authors read and approved the final manuscript.

Financial statement: This research received no specific grant from any funding agency in the public, commercial or not-for-profit sectors.

Conflict of interest: Authors declare no conflict of interest.

Ackownledgments

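### The side-effect outcome depends on attributing events to treatment, but no described role is both placed and assigned to do so, so OMT harms are liable to be under-recorded

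*Protocol*

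**What the plan says.** All references are to the protocol.

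- **Measurements, Secondary outcomes, item 8** is "side effects of treatment (osteopathy and clinical procedures". Items 2 to 5 of the same list count events per day whatever their cause.
- **Allocation concealment and blinding** says that "NICU staff are unaware of study design and outcomes" and that "NICU staff are blinded to patients allocation, since all infants will be touched by osteopaths from group A and B".
- **Data entering and data export** divides the software into three sections, each open only to its own user group. Section 1 is "Intended for use by neonatologists and nurses for recording patients' general details and all clinical information". On timing: "Nursing and medical records will be collected daily by the NICU staff, from the time the infants enters the unit to the time of discharge". Treating osteopaths, in section 2, "will collect data in relation to the structural examination and the techniques applied". Evaluating osteopaths, in section 3, "will only collect data for the structural examination".
- **Research investigators** keeps the evaluating osteopaths ignorant of allocation. **Intervention provided into the trial** says that the treating osteopaths take no part in design, data entry or analysis.
- **Ethics and dissemination** states that "no potential side effects due to osteopathic care are predicted". The next sentence commits to recording any side effect during the study and discussing it in the final paper.

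**The concern.** An outcome worded as side effects of treatment needs two pieces of knowledge in one place: that a clinical event happened, and that it can be linked to what was done to the infant. The protocol's division of roles and its closed record sections keep these apart. The commitment in the ethics section names no recorder, and it follows a statement that none are expected.

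What is at stake is the trial's ability to say anything about harm. An episode of apnoea or bradycardia after handling could be entered in section 1 as ordinary prematurity and never reach item 8. The paper could then report no side effects when the finding reflects the recording route and not the treatment. Meanwhile the data that would support a fair comparison, blinded daily records in both arms, would go unused for this purpose.

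**Working it through.** **1. Who can see events, and who can link them to OMT while the infant is on the unit**

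| Role | Sees clinical events daily? | Knows who received OMT? | Stated duty to record side effects? |
|---|---|---|---|
| NICU staff (section 1) | Yes, both arms | No, blinded | Not named; they record all clinical information |
| Treating osteopaths (section 2) | No access to section 1; on the unit Tuesdays and Fridays | Yes | None listed |
| Evaluating osteopaths (section 3) | No access to section 1 | No | None; examination data only |
| IT consultant (randomisation) | No such role described | Yes | None |
| Statistician | Only after export at the end of the study | Can link records after export | None described |

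No row has yes in all three columns. The statistician can join events to arm after export, but that allows a comparison of arms, not a judgement about the cause of a single event.

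**2. What the other outcomes already cover**

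Vomiting, regurgitation and time to full enteral feeding (items 2, 3 and 6) are counted regardless of cause, and the Statistical analyses section applies its model to the secondary endpoints. Feeding intolerance is therefore largely covered. Apnoea and bradycardia appear only in the discharge conditions listed under the primary outcome. They are not an outcome in their own right.

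**3. What a count of zero would mean**

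The protocol gives no safety figure to reproduce. The one document input is 345 infants per group (Sample size).

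- Upper 95% limit with zero events in 345: rule of three, 3/345 = 0.87%; exact one-sided, 1 − 0.05^(1/345) = 0.86%. Either holds only if every event is captured.
- Assume that 1% of treated infants have an OMT-caused event: 345 × 0.01 = 3.45 expected. With capture fraction c, also assumed, P(none recorded) = (1 − 0.01c)^345.

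| c | Expected recorded | P(none recorded) |
|---|---|---|
| 1 | 3.45 | 0.03 |
| 0.75 | 2.59 | 0.07 |
| 0.50 | 1.73 | 0.18 |
| 0.25 | 0.86 | 0.42 |
| 0 | 0 | 1 |

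The meaning of a zero thus rests on c, and nothing in the protocol allows c to be estimated.

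**4. What an all-cause comparison could detect**

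Assume 10% of controls have a given event, 345 per arm, 80% power, and the protocol's α = 0.01 taken as two-sided (sidedness is not stated). With an average proportion of 0.145:

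(2.576 + 0.84) × √(2 × 0.145 × 0.855 / 345) = 3.416 × 0.0268 = 0.092, or about 9 percentage points.

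**The case against.** The strongest reply is that this is missing detail and not a flaw. Section 1 holds all clinical information daily in both arms, so events are not lost, and blinding of the recorders protects against unequal ascertainment. Event lists and causality procedures are often left to a SAP or study manual, and item 8 itself states no judging rule. Staff also know that osteopaths handle every infant, so they could flag an event as following a session without knowing the arm.

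Much of this stands, and it limits the point. A reader might infer any of the following, and the document does not support them:

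- **Harms will be undercounted by construction.** Not shown. Events can be in section 1 whatever cause is assigned, and the ethics section does promise that side effects will be recorded. The supported statement is that harms are liable to be under-recorded under item 8.
- **Osteopaths record only examination and techniques.** The word only is applied to the evaluating osteopaths. For the treating group, side effects are simply not among the listed data.
- **Controls cannot have an osteopathy side effect.** They receive a 10-minute hands-on evaluation on the same schedule, and item 8 also covers clinical procedures, which occur in both arms. What controls cannot have is an effect of the manipulative treatment itself.
- **NICU staff know nothing of the design.** The protocol says so, but the ethics section has a neonatologist explain the information sheet to parents, and Participating NICUs names neonatologists among the principal investigators. This does not rescue item 8, because knowing the design without the allocation still does not show whether a session included treatment.

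The reply does not remove the point. The protocol describes no all-cause comparison from section 1 beyond the listed outcomes, and it gives nobody the task of flagging events after sessions. The roles and access rules that it does fix work against the outcome that it names.

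**Conclusion.** The point holds in a limited form. Item 8 depends on attribution. The staff who see events are blinded, and the osteopaths who know allocation cannot see the clinical records and have no listed duty to report side effects. OMT-related harms outside the existing outcomes, with apnoea and bradycardia the clearest example, are liable to be under-recorded. A report of no side effects could not be interpreted: the upper limit of about 0.9% for zero in 345 presumes complete capture, which the protocol gives no reason to assume.

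The amount of any undercount cannot be stated. The 3% to 42% range for capture between 100% and 25% rests on an assumed 1% true rate and measures no bias in this trial. The primary outcome is untouched. This should be changed, because the present wording passes over a fairer comparison that the planned records would largely allow.

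**What to change.** Define outcome 8 as clinical adverse events irrespective of judged cause, taken from the blinded daily section 1 records over the whole stay in both arms. Name the events in advance, including apnoea and bradycardia. Report counts, the difference and its confidence interval by arm. List separately any event noted during an osteopathic session in either arm, and say who records it.

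Reconcile Data entering and data export, Secondary outcomes item 8, and the side-effect statement in Ethics and dissemination, so that the promise to record side effects has a named recorder and a place in the database. The claim that staff are unaware of the design should be squared with the neonatologists' part in consent and as investigators.

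A fixed interval after each visit should not be the main analysis. Records are described as daily, so shorter windows may not be derivable, and sessions can be skipped in critically ill infants, so such windows would tend to miss their worst days. Whole calendar days could serve as a supplementary analysis.

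The cost is mainly protocol and analysis wording, since the daily records are already planned in both arms; the session list needs a small addition to sections 2 and 3. The downside is a longer table with many events unrelated to OMT, and limited power: about 9 percentage points detectable from an assumed 10% control rate. The results should therefore be read as estimates with intervals, not as proof of safety.

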Osteopathy is a form of drug-free non-invasive manual medicine, designated as complementary and alternative medicine (CAM). It relies on manual contact for diagnosis and treatment 12. It respects the relationship of body, mind and spirit in health and disease; it lays emphasis on the structural and functional integrity of the body and the body's intrinsic tendency for self-healing. Osteopathic practitioners use a wide variety of therapeutic manual techniques to improve physiological function and/or support homeostasis that has been altered by somatic (body framework) dysfunction (ICD-10-CM Diagnosis Code M99.00-09), i.e. impaired or altered function of related components of the somatic system; skeletal, arthrodial and myofascial structures; and related vascular, lymphatic, and neural elements 13.

Osteopathic practitioners use their understanding of the relationship between structure and function to optimize the body’s self-regulating, self-healing capabilities. This holistic approach to patient care and healing is based on the concept that a human being is a dynamic functional unit, in which all parts are interrelated and which possesses its own self-regulatory and self-healing mechanisms. Two essential components of osteopathic health care are the structural evaluation of the patient for diagnosis and an array of manipulative techniques for treatment 12.

Aim of the structural examination is to locate somatic dysfunctions, while the array of manipulative techniques are used to relieve tissues tensions, improve blood flow and lymphatic drainage.

Although several studies document the effect of osteopathic manipulative treatment (OMT) in a population of pediatric patients 14-16, the medical literature lacks information about any potential benefits of the use of OMT in preterm infants. The only study published demonstrated a potential positive effect of OMT in reducing the likelihood of excessive LOS and gastro-intestinal symptoms 17.

Aim of this multicentre randomized controlled trial is to examine the association between OMT and LOS in a larger population.

METHODS AND ANALYSIS

Aim of the study

Primary outcome is to evaluate the effectiveness of OMT in reducing LOS in a sample of premature infants.

Secondary outcome of the study is to evaluate the difference in daily weight gain, number of episodes of vomit and regurgitation, stooling, use of enema, time to full enteral feeding (nipple and/or bottle) and NICU costs.

Study type

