Statistical analyses will take into account the intention-to-treat analysis. Missing data will be handled using last observation carried forward (LOCF) imputation technique. Arithmetic means and standard deviation will be used for the general characteristics of the study population. Univariate statistical tests will be performed to compare the experimental group and control group at the baseline. A generalized linear model, linear regression, will be considered to study the independent effect of OMT on primary endpoint and secondary endpoints, taking into account all possible confounders. The significance level will be at α=0.01. Differences between the groups will be presented as mean with 95% CI or in categories with OR for categorical data.

The statistical program in use for randomization and data analyses is R 18.

Sample size

Sample size calculation used an effect size of 0.3 calculated from previous studies, considering a mean difference of 4 days between experimental and control group and a SD of 14. The statistical power is set at 0.90 and an alfa level equal to 0.01. This produces a sample size of 333 per group. To prevent loss of power, the sample size is increased up to 345 subjects per group. The whole sample (N=690) is then divided, with a final result of N=230 preterm infants for each NICU. A longer period of study enrollment has been considered a strategy to achieve the estimated sample size.

Coordinating center

The coordinating center EBOM consists of an executive division, President and Vice-President, an administration office, a group of researchers, an information technology consultant and a senior biostatistician.

The coordinating center collaborates with the A.I.O.T. - Accademia Italiana Osteopatia Tradizionale.

ETHICS AND DISSEMINATION

During the routine initial post-delivery consultation, the neonatologist approaches parents or legal guardians explaining the patient information sheet. Written informed consent will be then obtained from the above-mentioned guardians at study enrollment. Participation is voluntary and data collected will be sent to the coordinating centre using an anonymous identification for each patient.

The trail is approved by the ethical committee of Macerata hospital (n°22/int./CEI/27239) and it is under review by the other regional ethics committees. Moreover the trial has been registered on clinicaltrial.gov (identifier NCT01645137).

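### LOCF, the protocol's only missing-data rule, has no valid meaning for length of stay, and T1 is not defined for infants who die or are transferred

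*Protocol*

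**What the plan says.** The Protocol's Statistical analyses section states the analysis principle, "Statistical analyses will take into account the intention-to-treat analysis", and then the rule for gaps in the data: "Missing data will be handled using last observation carried forward (LOCF) imputation technique". The abstract repeats the rule. Neither place exempts the primary outcome or names another method.

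The section on the primary outcome says: "LOS will be used as primary outcome and measured as the mean difference in days between T1 and T0". Under Measurements, the closing time point falls "at the end of the stay in the unit (discharge time, T1". The physiological conditions required for discharge are listed, but nothing says what T1 is for an infant who leaves the unit without meeting them.

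The direction of benefit is set under Aim of the study: "Primary outcome is to evaluate the effectiveness of OMT in reducing LOS in a sample of premature infants". NICU cost is defined under Secondary outcomes as a daily expense multiplied by LOS. The planned model for primary and secondary endpoints is a linear regression; no censoring or competing event is mentioned.

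Two further statements matter. The section on data entry says: "Nursing and medical records will be collected daily by the NICU staff, from the time the infants enters the unit to the time of discharge". The exclusion list under Population includes infants transferred to or from another hospital.

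**The concern.** Last observation carried forward needs a series of earlier measurements of the same variable. LOS has none, because it exists only once the stay is over. If the rule is applied anyway, something must stand in for the missing duration. The candidates are the days accrued up to the last record or the value at entry, which is 0 days. Both are shorter than the completed stay would have been. Since a shorter stay is the benefit sought, an infant with an incomplete stay enters the primary analysis as a good result, and cost follows.

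Two gaps beside the LOCF sentence push the same way or cloud the analysis set. If T1 is simply the end of the stay in the unit, a death has a T1 and yields a short LOS without any imputation. And transfer out can be known only after entry, so removing such infants because of the exclusion list contradicts intention to treat, while keeping them leaves their LOS without a rule.

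At stake are the validity of the primary comparison if exits differ by arm, and some loss of effect and power if they do not.

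**Working it through.** **Plan's own figure.** The Sample size section gives effect size 0.3, alpha 0.01 and power 0.90, with 333 per group. Taking alpha as two-sided (the Protocol does not say), the normal formula gives n = 2 × (2.576 + 1.282)² / 0.3² ≈ 331. The t-test version gives 332.3, hence 333, so the figure is reproduced. (The stated 4 days and SD of 14 give 4/14 = 0.286, not 0.3. That is a separate matter.)

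**Inputs from the Protocol.** SD 14 days, target difference 4 days, 345 per arm after the allowance, alpha 0.01. The allowance is 345 − 333 = 12 per arm, or 12/345 = 3.5%. No rate of death, transfer or withdrawal is given. On the duration of stay: "An expected average period of 4 weeks has been considered", that is, 28 days.

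**Assumptions not in the Protocol.** The excess of early exits in one arm is 6 infants (for example 12 against 6) or 12 infants (12 against 0). Each such stay is recorded 14 to 20 days too short. The excess is systematic, and the bias acts as a pure shift.

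**Standard error.** SE = 14 × √(2/345) = 1.066 days.

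**Shift and error.** Shift = excess share × days cut off. Error with no true effect = Φ(shift/SE − 2.576) + Φ(−shift/SE − 2.576).

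| Excess in one arm | Days cut off | Shift (days) | Share of 4 days | Two-sided error |
|---|---|---|---|---|
| 6/345 = 1.7% | 14 | 0.24 | 6% | 0.012 |
| 6/345 = 1.7% | 20 | 0.35 | 9% | 0.014 |
| 12/345 = 3.5% | 14 | 0.49 | 12% | 0.018 |
| 12/345 = 3.5% | 20 | 0.70 | 17% | 0.028 |

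**Equal loss in both arms.** Suppose 3.5% in each arm are recorded at 7 days instead of 28.
- A true 4-day effect becomes 4 × (1 − 0.0348) = 3.86 days.
- The variance becomes 0.9652 × 14² + 0.0348 × 0.9652 × 21² = 189.2 + 14.8 = 204.0, so the SD is 14.3.
- Power at 345 per arm falls from 0.880 (4 days, SD 14) to 0.835.
- No false benefit arises; the effect is diluted.

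**Which exits each rule touches.**
- Death: on the wording of T1 the stay has ended, so LOS is not missing. The short value comes from the T1 definition, and replacing LOCF alone would not cure it.
- Withdrawal from osteopathic treatment: unit staff still record daily to discharge, so LOS is known. It is missing only if use of the data is withdrawn too.
- Transfer after entry: the infant is either dropped (against intention to treat) or kept with an incomplete LOS. The Protocol does not say which.

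**The case against.** The strongest reply is that LOCF may seldom reach the primary outcome. As set out above, a death has a T1, a withdrawn infant usually still has a discharge date, and a transferred infant may be excluded. Eligible infants are also at least 29 weeks and free of medical complications, with admissions for comfort care excluded, so early exits are probably few. This stands as a limit on size. It does not give LOCF a meaning for LOS, and it shows that the T1 wording and the transfer exclusion need repair as well.

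A reader might infer several stronger points, which the Protocol does not support:

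- *That LOCF itself turns deaths into short stays.* That runs through the T1 definition.
- *That any imbalance in exits creates a spurious effect.* Chance imbalance is already covered by the standard error. Error rises only if treatment changes who leaves early or when. Nothing in the Protocol suggests this, and it plans to blind unit staff. The bias would favour osteopathic treatment only if early exits were commoner or earlier in that arm.
- *That the error reaches about 5%.* This needs a 1.0-day shift, for example a 5% excess cut short by 20 days. That is about 17 infants (0.05 × 345) more in one arm than the other, above the whole allowance of 12.
- *That weight gain on missing days is set to exactly zero.* The outcome is "daily weight gain, referred as the net weight variation per day expressed in grams". Carrying that variable forward repeats the last gain. Zero follows only if raw weight is carried forward, which the Protocol does not say.
- *That standard errors for LOS are understated.* In the equal-loss example truncation widens the SD. The single-imputation problem belongs to the daily outcomes and is small at about 3.5% missing.

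**Conclusion.** The point holds and should be fixed. The Protocol itself prescribes LOCF for all missing data, so this is not a detail left open for a later analysis plan. For LOS no reading of the rule gives a valid value, and every workable one errs towards a short stay. The handling of deaths through T1, and of infants transferred after entry, is a separate gap that must be closed with it.

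The likely size is modest. The 0.24 to 0.70 days and the error of 0.012 to 0.028 depend on the assumed excess and truncation. The upper end puts the entire 3.5% allowance in one arm and none in the other. Without a systematic difference between arms the consequence is dilution and some loss of power.

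**What to change.** - Delete LOCF from the abstract and from Statistical analyses.
- Take LOS for every randomised infant, including those withdrawn from osteopathic treatment, from the unit's own records.
- Define T1 as discharge alive, so that death is not counted as discharge, and state how deaths enter the primary regression. Add time to discharge alive, with death as a competing event, as a stated sensitivity analysis. Giving deaths the longest observed LOS is not recommended, because it puts arbitrary extreme values into a regression of means.
- Keep infants transferred after entry in the intention-to-treat set, with LOS treated as incomplete at transfer, and reconcile the exclusion list with this. Counting days at the receiving hospital would change the endpoint from stay in the unit to total hospital stay.
- Multiply impute LOS that is truly missing, from arm, centre, gestational age and birth weight. Derive NICU cost from the same LOS.
- Analyse the daily outcomes with a likelihood-based mixed model on the observed days, without imputation.

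The cost is revised wording and a little more analysis work; no new measurements are needed.
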